### Canadian Occupational Performance Measure (COPM) [56].

COPM is a semi-structured interview to capture the participant’s self-perception of everyday performance. Using 10-point scale participants are asked to identify and rate their performance and satisfaction from performance of three specific goals. The COPM has been found sensitive to change in the perceived occupational performance [57] and as a reliable and valid assessment for people with varied health conditions [58–60]. The COPM has been translated into Hebrew and used in other studies to assess daily performance e.g., [48, 49].

### Behavior and length of stay in TC

Information regarding participant behavior (discipline, number of times being late for scheduled activities) will be collected from the TC counselors. Length of stay (days) residing in TC. The Longer time spent in the TC, the better**.**

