**Methods:**

Forty-eight participants from a community of men in a TC, aged 18–45 years will be randomly allocated to (i) F-CaST—(experimental group) providing sensory and EF strategies for improving daily function; (ii) standard care (control group) as provided in the TC. Assessments will be conducted by assessors blind to group allocation at 4 time points: T1- pre-intervention; T2- post-intervention; T3- 1-month follow-up; and T4- 3-month follow-up. Primary outcome measures will be everyday performance, assessed by the Canadian Occupational Performance Measure (COPM), behavior and length of stay in the TC; secondary outcome measures will assess EF, SMD. Semi-structured in-depth qualitative interviews will be conducted at T1, T2 and T4.

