## Setting

An adult community of men, within a TC. The TC is a rehabilitation center providing a controlled drug free environment with multidimensional support for individuals with severe SUD. Treatment in the TC is hierarchal, based on the duration and progress of the residents and usually lasts 1–1.5 years. The abstinence of the residents is routinely verified through random urine testing**.** Only individuals with the diagnosis of severe SUD (drug and/or alcohol use) and with no dual diagnosis are accepted into this TC. Diagnoses is done by a psychiatrist according to the Diagnostic and Statistical Manual of Mental Disorders-IV (DSM-IV).

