### Quantitative outcome measures

#### Primary outcomes measure

Every-day performance in the TC; Behavior and length of stay in the TC.

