## Data analysis

Descriptive statistics will be used to describe the participants in each group, in terms of their, demographic information and SUD parameters, primary and secondary outcome measures. Pre-intervention differences between the two groups will be analyzed using t-Test for independent samples (continuous measures) or Chi square (dichotomous measures). A repeated measures ((2)X4) analysis of variance ANOVA will be used to compare within- and between- group scores, for time (T1, T2, T3, T4) comparing the F-CaST to standard care and for interaction time*group effect.

To assess the clinical meaningfulness of the outcomes, the Partial Eta squared in ANOVA effect size will be calculated. Partial Eta squared is interpreted as the proportion of the total variability in the dependent variable that is accounted for by variation in the independent variable. ANOVA Partial Eta squared of 0.01, 0.06 and 0.14 are considered small, medium and large effect sizes (respectively).

Statistical significance will be set at p < 0.05, and all analyses will be conducted using SPSS for Windows version 27.0 (SPSS Inc, Chicago, IL). The transcripts of each of the four in-depth interviews will be analyzed using content analysis (an initial review, the development of mapping categories, and the building of a mapping categories tree) [77].

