## Discussion

The aim of this mixed-method single-blind randomized controlled trial is to examine the efficacy of the Functional Cognitive and Sensory Treatment (F-CaST), an innovative personalized therapy in men with SUD residing in a TC. We expect that the F-CaST will lead to improved everyday performance and longer length of stay in the TC, compared to the control group. If the F-CaST will show to be effective, cognitive and sensory strategies may be incorporated as an adjunctive intervention in SUD rehabilitation and will support the need to provide intervention programs based on occupational performance to SUD population. Moreover, we believe that the effectiveness of the intervention program will be found at each of the assessments, thus strengthening the effectiveness of the intervention program over time.

The following study limitations will need to be taken into account. The fact that only men with SUD will be recruited from a single TC, will limit the generalizability of the findings to women. Future studies utilizing the F-CaST should definitely include women preferably from therapeutic communities. F-CaST group will be compared to a control group, who will receive standard care, and not an active control group. The duration of the intervention is short and therefore we might not be able to demonstrate effectiveness.

We envision that F-CaST, which is a novel intervention, will show to improve rehabilitation outcomes of men with SUD. F-CaST will fill gaps in current rehabilitation and expand our.

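### Length of stay, a primary outcome, is fixed as raw days with longer scored as better, with no counting window and no named analysis that fits it

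*Protocol article*

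**What the plan says.** All places are in the protocol article.

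- **Rank.** The primary outcomes are given as "Every-day performance in the TC; Behavior and length of stay in the TC". The Discussion expects "longer length of stay in the TC, compared to the control group".
- **Definition.** The section on behavior and length of stay counts the days a man resides in the TC and adds only the scoring rule: "The Longer time spent in the TC, the better". It gives no start date, no end date, and no distinction between completing the programme and leaving early.
- **Programme.** Under Setting: "Treatment in the TC is hierarchal, based on the duration and progress of the residents and usually lasts 1–1.5 years".
- **Follow-up.** The last assessment is "T4- 3-month follow-up".
- **Analysis.** Under Data analysis: "A repeated measures ((2)X4) analysis of variance ANOVA will be used to compare within- and between- group scores", with time taken at T1 to T4. The other tests named there are for baseline only: "Pre-intervention differences between the two groups will be analyzed using t-Test for independent samples", and chi-square for dichotomous measures.

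**The concern.** Length of stay is one duration per man. It has no value at each of four visits, so the time effect and the time-by-group interaction are undefined for it. Entering the days accrued at each visit would not help: they rise with the calendar for every resident and simply stop for a man who has left.

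The scoring rule also needs a window to have a meaning. A stay can be short because a man walked out, because he finished, or because observation stopped. Raw days do not separate these. The Background motivates the trial by early departure from TCs, so the outcome should show whether F-CaST keeps men in treatment. As fixed, it may not, and the choice of window would be open after the data have been seen.

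**Working it through.** **1. Where T4 falls in a man's residency**

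Inputs: at most 21 days of residency at entry (Inclusion criteria); assessments within one week, 7 days (Procedure); T4 three months after the intervention, taken as 91 days. The length of the intervention is not given in weeks; the Discussion calls it short. I assume W = 4 to 16 weeks.

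Latest residency day at T4 = 21 + 7 + 7W + 91

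- W = 4: day 147
- W = 16: day 231
- To reach day 365: W = (365 − 119)/7 = 35.1 weeks

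The usual programme runs about 365 to 548 days. A man who has not left early is therefore normally still resident at T4.

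**2. Window A: total stay, data ending at T4**

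- If the 40% dropout under Sample size is assumed to mean leaving the TC by T4: 0.60 × 48 = 28.8, about 29 unfinished stays (60%).
- If the Background's upper figure of 71% is spread at a constant hazard over 365 to 548 days, counting from residency day 21, the share still resident at T4 is exp(−λt) with λ = −ln(0.29)/L. For L = 365 and t = 231 − 21 = 210 it is 49%. For L = 548 and t = 147 − 21 = 126 it is 75%.
- If all 71% leave before T4: 29%, about 14 of 48.

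**3. Window B: days counted to discharge**

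A completer at 12 months scores 365 and one at 18 months scores 548, a gap of 183 days against the faster man.

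Arm-level illustration, not a forecast:

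- Arm with 40% early departure, completers at 548 days: mean = 0.60 × 548 + 0.40 × m = 328.8 + 0.40m, where m is the mean stay of early leavers. With m about 176 days the mean is about 399.
- Arm with no early departure, completers at 365 days: mean = 365.

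The arm with perfect retention scores lower whenever m exceeds (365 − 328.8)/0.40 = 90.5 days.

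**4. Window C: days resident up to a common T4**

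Assume T4 is 120 days after randomisation, with exponential departure and 40% of controls gone by then: λ = −ln(0.60)/120 = 0.00426 per day.

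- Control mean = (1 − 0.60)/λ = 94.0 days
- Hazard ratio 0.5: survival at day 120 = √0.60 = 0.775; mean = (1 − 0.775)/(λ/2) = 105.9 days

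These are restricted means. The difference of 11.9 days is valid and fully observed if departure dates are known. It is small only because the window is short.

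**5. What an event-based analysis could detect**

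Schoenfeld formula, 1:1 allocation, two-sided 0.05, 80% power: ln HR = −(1.96 + 0.84)/√(0.25 × events).

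- 40% of 48, about 19 events: HR = exp(−2.80/2.18) = 0.28
- 71% of 48, about 34 events: HR = exp(−2.80/2.92) = 0.38

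The stated 24 per group cannot be reproduced for this outcome. The calculation rests on COPM alone and gives neither the difference nor its SD.

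**The case against.** The strongest defence is that this is a condensed article. Its ANOVA sentence concerns scores at four visits and never says that length of stay will be analysed that way; the test may stand in a fuller document. That is fair as far as it goes: the article does not expressly assign ANOVA to this outcome. But it names no other post-baseline comparison for a primary outcome, and the definition and scoring direction are its own words. Those are fixed badly, not merely left out.

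Longer-is-better is also reasonable as a retention proxy before anyone can complete, and days resident to a common T4 would be a sound measure. Both points stand. The article, however, states no such window.

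A reader might infer more than the text supports:

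- **That both harms act together.** They belong to different windows. Up to T4 almost nobody has completed; to discharge, T4 cuts nothing off.
- **That everyone resident at T4 is necessarily censored.** T4 is an assessment visit, and nothing says the counting of days stops there.
- **That 40% will have left by T4.** The dropout figure has no date and need not mean leaving the TC; a man could stop assessments and stay resident.
- **That 94 against 106 days shows bias.** It does not.
- **That F-CaST will speed completion.** Nothing says so; the 183 days compares the two ends of a usual range, not the arms.
- **That residency before randomisation biases the result.** It is limited at entry and balanced in expectation, so it adds noise, not bias.

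**Conclusion.** The point holds in conditional form. Two parts do not depend on any dropout rate: the counting window is undefined, and the only outcome analysis named cannot handle one duration per man. The consequence depends on the window chosen:

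- **Total stay with data ending at T4:** stays are incomplete for about 60% of men under the assumption that the 40% means departure by T4, and for about 29–75% across the scenarios above. That most stays are unfinished is likely but not established.
- **Days to discharge:** the rule puts a 12-month completer about 180 days below an 18-month one, and an arm with better retention and faster completion could score worse.

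The timeline rests on an assumed intervention of 4 to 16 weeks, but the conclusion that T4 precedes usual completion holds up to about 35 weeks. Because this is a primary outcome and an explicit hypothesis, the definition should be settled before outcome data are examined.

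**What to change.** Define the outcome as time from randomisation to unplanned departure from the TC, up to one fixed common horizon: T4, or a later common date. Do not count planned completion as failure. Include all 48 randomised men, whether or not they attend later assessments, and censor at the horizon those who have not left early.

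Name one main analysis: either a log-rank test stratified by ADHD, matching the randomisation, or the restricted-mean difference in days resident to the horizon with its 95% CI. Show Kaplan-Meier curves as description. If the horizon extends past the earliest usual completion, treat completers as retained to the horizon in the restricted mean; otherwise the reversed ranking returns. State that the repeated-measures ANOVA applies only to measures taken at T1 to T4.

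The cost is revised wording plus a recorded departure date and reason for every man. The change makes the result interpretable, not well powered. With about 19 events only a hazard ratio near 0.28 would have 80% power (about 0.38 with 34 events), so the result should be reported mainly as an estimate with its CI, and a non-significant test should not be read as no effect on retention.

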### Secondary outcome Measures

EF, sensory modulation, self-efficacy, life satisfaction, and use of strategies. We selected a variety of assessments to assure that we can capture many aspects of this novel intervention.

In-depth qualitative interviews will also be performed to provide additional insight related to the perceived link between EF, SMD and daily functioning in the TC.

### Executive functioning

Several tools will be used to assess EF in this population who may have  deficits in EF but are overall high functioning within the TC. EF in everyday situations via self-report will be assessed as well as neuropsychological tests specifically assessing planning, inhibition, and working memory.

### Color trails test (CTT) [60].

A pen and paper neuropsychological test used to measure cognitive flexibility, working memory and processing speed. The CTT includes two parts: (1) CTT 1 requires connecting a series of 25 numbered circles that are scattered on a sheet of paper and (2) CTT2 requires connecting numbered circles from 1 to 25 in sequence alternating between two colors—pink and yellow (e.g.,1-pink, 2-yellow, 3-pink, 4-yellow). The time (seconds) to complete each part is recorded. Less time indicates better performance. Completion time (up to 240 s) is translated to standardized score by normative data correcting for age and years of education. The CTT is widely used and is valid and reliable in a variety of populations [62].

### The Cambridge automatic neuropsychological test battery (CANTAB) [63, 64].

A computerized task (using a touchscreen tablet) will be used to assess multitasking. The **Multitasking Test (MTT) **[22] assesses participant’s ability to use multiple sources of potentially conflicting information to guide behavior. Arrows appear on the right or left side of the screen and participants receive instructions varying between "direction" and "side" for each trial. Some trials display congruent stimuli (e.g., arrow on the right side pointing to the right) whereas other trials display incongruent stimuli, which require a higher cognitive demand (e.g. arrow on the right side of the screen pointing to the left). The MTT was found with reasonable sensitivity (82.8%) and specificity (74.5%) for mild cognitive impairment [65]. The number of errors (Total incorrect), the median duration of the response time and the Multitasking Cost (difference between the median response time in the part where two rules are followed alternately and the one where one rule is followed) will be analyzed.

### Behavior rating inventory of executive function-adult version (BRIEF-A) self-report and informant report forms [66]

This 75-item questionnaire assesses EF in everyday situations referring to the past 30 days. The items graded on a 3-point scale: 'never', 'sometimes' or 'always' are summed-up into nine clinical scales which form two indices: the Behavioral Regulations Index (BRI), and the Metacognition Index (MI) and together produce an overall Global Executive Composite score (GEC). Raw scores are converted to T-scores where a score of 65 or higher denotes a clinical deficit. The three indices of the BRIEF-A have been shown with excellent internal consistency (Cronbach’s α: 0.93–0.94) and one-month test–retest reliability (r = 0.93–0.94), high ecological validity [66] and have been used as a sensitive measurement in patients with SUD [66].

### Sensory modulation

#### The Sensory Responsiveness Questionnaire-Intensity Scale (SRQ-IS) [68].

This standardized self-report questionnaire aims to clinically classify SMD in adults. Items represent typical daily life situations involving auditory, visual, gustatory, olfactory, vestibular and somatosensory sensations, excluding pain. Items are phrased either in a hedonic or aversive valence and are graded on a 5-point Likert scale: 'not at all' (1) to 'very much' (5) The SRQ provides two scores for each of the two SMD subtypes: SMD-SOR is determined by applying the SRQ-Aversive subscale score for scores higher than the normal cut-off score (mean + 2SD; 1.87 + 0.52); the SMD-SUR subtype is determined by applying the SRQ-Hedonic subscale score for scores higher than the normal cut-off score (mean + 2SD; 2.10 + 0.66). The SRQ been demonstrated to have test–retest reliability (r = 0.71–0.84; *p* < 0.001–0.005), internal consistency (Cronbach α = 0.90–0.93) and construct and criterion validity [68].

#### Self-efficacy

##### The New General Self-Efficacy Scale (NGSE) [69].

A self-report questionnaire to measure individual’s perceived capacity to achieve their goals despite their difficulties. Each of the eight statements (e.g. “Even when things are tough, I can perform quite well”) are rated using a 5-point rating scale: 'strongly disagree' [1] to 'strongly agree' (5). Higher scores indicate higher self-efficacy. The NGSE scale has high reliability and construct validity [68].

##### The Satisfaction from the intervention questionnaire [68, 71].

Following the F-CaST intervention, participants from the experimental group will be asked to rate their general and specific satisfaction from the intervention (e.g., How much did the intervention motivate you to make an effort?). Additional feedback will be also obtained (for example, was the intervention too long/just the right length/too short?). Each of the 9-items are rated separately. The questionnaire has been previously used to assess satisfaction in feasibility studies [70, 71].

##### Demographic questionnaire

Demographic data (age, years of education, employment status), information regarding substance consumption patterns [25] and health information will also be collected.

##### Qualitative data

Qualitative data will include a semi-structured interview and the use of strategies will be assessed.

#### Semi-structured interviews

Semi-structured interviews will provide a deeper understanding of the perspectives of the individuals with SUD and specifically to understand how adults with SUD perceive their everyday performance at the TC, the link between their performance to EF and to SMD deficits (See interview guide in Table 1). The interviews will be conducted pre and post-intervention (T1 and T2) and 12-weeks follow-up (T4). The interviews will be conducted by an  occupational therapist, not involved in the study, in a quiet room. The qualitative interviews will be audio-recorded, transcribed-verbatim and analyzed using content analysis.

**Table 1 Tab1:** The semi-structured interview guide

Questions	Description
Experience in therapeutic community	Can you tell us about your experience in the TC? (Simplified question: How do you feel here? What is your opinion of this place and the people around you?)
Perception of the environment (physical and personal environment)	How do you feel within the TC? (To simplify or make it more detailed: For example, the people around you (counselors, other members) as far as the physical surroundings are concerned (the room, the building, dining room). If it is difficult to answer: Can you compare the TC to your previous living accommodations? How is it different? How does it make you feel?
Goals	What are the daily goals in your rehabilitation process? What challenges have you recognized in regards to your stay in the community? What will help you function in the community? (For instance, when you look ahead at your stay here, what do you think will be challenging?)
Strengths and weaknesses (events and coping mechanisms)	Tell me about an event or something that happened in the past week that you perceived as challenging. What happened? How did you deal with it?
Concept of function (supporting and restrictive factors in daily function)	As you approach the end of your stay, please tell me what in your functioning or your surroundings helped you remain in the community? Were there any occurrences that caused you to think about staying or leaving? Please give me an example What do you think would help you stay in the community going forward? Please relate to all the factors surrounding you in the community. What could possibly delay or cause your leaving the community?

##### The Self-Regulation Skills Interview (SRSI)[71].

A semi-structured interview to evaluate meta-cognitive abilities using a difficulty identified by the participant. Individuals are asked six questions relating to the identified difficulty. Emergent awareness: “Can you tell me how you know that you experience [the difficulty]?” Anticipatory awareness: “When are you most likely to experience [the difficulty], or in what situations does it mainly occur?”; Motivation to change: “How motivated are you to learn some different strategies to help overcome [the difficulty]?” (A self-rating between 0 and 10 was obtained); Strategy generation: “Have you thought of any strategies that you could use to help cope with [the difficulty]?”; Strategy selection: “What strategies are you currently using to cope with [the difficulty]?”; Effectiveness of strategies: “How well do the strategies that you are using work for you?” Each question is rated using a 10-point scale (0 = very high to 5 = moderate to 10 = very low) where scores reflect the level of awareness, motivation, strategy knowledge, or use of strategies. An average score is obtained, lower scores indicate better use of strategies. The SRSI has established interrater reliability (0.83 < α < 0.92); test–retest reliability (0.69 < α < 0.91) and concurrent validity [71].

## The interventions

### The F-CaST

The Experimental group will receive F-CaST, which focuses on teaching and practicing the use of strategies to compensate for deficits in EF and sensory modulation deficits to improve their daily performance. Participants will be provided with knowledge regarding their EF and sensory modulation difficulties in order to increase their awareness and understanding of how these deficits impact their daily function.

The F-CaST is based on the Functional and Cognitive Occupational Therapy (FaCoT) intervention which was developed for individuals with mild stroke, experiencing deficits in EF and emotional-behavioral symptoms [49]. The FaCoT was based on theoretical models from the field of cognitive rehabilitation and Bandura’s social learning theory. The aspects of FaCoT of teaching and practicing the use of cognitive and behavioral strategies to improve daily functioning and participation, were integrated into the F-CaST. The integration of the SMD field (based on the Ecological Model of SMD [51]), is novel, creating the F-CaST intervention. See Table 2 for additional details regarding the individual and group sessions.

**Table 2 Tab2:** Description of F-CaST intervention

Content	Activities to facilitate learning
*Group sessions*	
Psychoeducational knowledge about the following topics which are then implemented in the individual sessions: - SUD and the impact on the brain - Reframing and conceptualizing function within the TC - Executive functions - Sensory modulation - The importance of executive functions and sensory modulation for efficient daily functioning in the TC - Strategies to overcome executive function deficits and for sensory modulation difficulties Sharing everyday situations according to the terms discussed The relation between Self-regulation and executive functioning in daily function	Group activities to encourage introspection to daily events through functional conceptualization Games and video clips that simulate different experiences that require executive functions or sensory modulation. Game-like activities to experience the effective use of strategies (in general) and specific executive functions or sensory strategies to overcome deficits Following these activities, sharing, reflecting on each self and others and group discussions will take place
*Individual sessions*	
The Psychoeducational knowledge that will be taught in the group sessions will be implemented to help each participant set their specific goals	Activity task analysis will be conducted regarding daily occupational goals that will be set by the participants For the first goal, both OT and participant will analyze and identify the specific difficulty within that goal Then an appropriate cognitive strategy will be selected to compensate for their EF deficits and promote their occupational performance. In addition, sensory strategies will be taught and integrated Cognitive strategies: Response inhibition, Initiation, Planning and Decision-Making Sensory strategies: Adjusting arousal levels and Self-regulation in the TC environment Behavioral strategies Self-perception, Situation interpretation and Future prediction will be taught and practiced using a positive persona (with high self-efficacy) and a negative persona (with low self-efficacy) in different everyday scenarios chosen as similar to each participant's goals After 3–4 sessions, the same process is done for another occupational goal and another cognitive strategy will be taught and practiced along the sensory and behavioral strategies

